### 2.8. Outcome Parameters

Serum hsCRP level will serve as the primary outcome parameter in this study. The levels of other inflammatory mediators, including IL-6, TNF*α*, VCAM-1, CD40 and soluble CD40 ligand (sCD40L), MCP-1, and MMP-9, as measured by enzyme-linked immunosorbent assay (ELISA), will constitute secondary outcome parameters. Additional secondary parameters will include safety and the extent of improvement in angina and BSS symptoms. 

To assess safety, patients will be asked to report any side effects or changes in feelings that they have noticed since the previous phase of data collection. In addition, the results of routine blood, urine, and stool tests, liver and kidney function tests, coagulation tests, and electrocardiogram tests will also be considered in the evaluation of safety. Finally, the clinical researchers will carefully monitor all patients for the potential onset of adverse events, the most severe of which may include arrhythmias, heart failure, recurrent myocardial infarction, myocardial rupture, cerebral infarction, cerebral hemorrhage, sudden cardiac death, and all-cause death. 

To assess improvement in angina symptoms, a scoring system will be applied based on the frequency, duration, and intensity of angina episodes [15, 16]. Similarly, a scoring system will also be used to evaluate BSS based on changes in signs and symptoms such as angina, a pulse of choppy or knotted nature, ecchymoses, dark purple tongue, lips, and gums, and expanded sublingual veins [17].

### 2.9. Data Collection Phases

Table 1 indicates the data to be collected at each phase of the study. At Phase I, before treatment for the trial is initiated, each patient's full medical history will be recorded, along with vital signs, symptoms of present illness, and all current medications. Tongue and pulse examination will be performed by experienced TCM physicians. Laboratory tests will include routine blood, urine, and stool tests, an electrocardiogram, an hsCRP test, and various other tests measuring cardiac markers (creatine kinase, CK-MB; troponin T, cTnT; troponin I, cTnI), liver and kidney function, blood lipid and glucose, and coagulation. A 10 mL blood sample will also be collected from each patient, centrifuged, and stored at −80°C for subsequent measurement of other inflammatory mediators (IL-6, TNF*α*, VCAM-1, CD40, sCD40L, MCP-1, and MMP-9) at the end of the study. Finally, the severity of each patient's angina and BSS symptoms will be quantitatively scored.

Phase II marks the end of the 14-day treatment period, at which time the medications specific to this study (i.e., simvastatin and STS) will be discontinued and the patients reassessed. Again, vital signs, symptoms of present illness, tongue and pulse exam results, and all current medications will be recorded. Angina and BSS scoring will be repeated, along with all Phase I laboratory tests aside from those measuring cardiac markers and blood lipid and glucose. As in Phase I, a blood sample from each patient will be collected and preserved for subsequent analysis of secondary inflammatory factors at the end of the study. A preliminary, nonstatistical evaluation of treatment safety and efficacy will also be performed by the data collectors.

Thirty days after simvastatin and STS are discontinued, Phase III data will be recorded, including level of hsCRP, angina and BSS scores, vital signs, symptoms of present illness, tongue and pulse exam results, and all current medications. As before, a blood sample for analysis of secondary inflammatory factors will be collected, and treatment safety and efficacy will again be preliminarily evaluated.

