### 2.5. Randomization and Blinding

A member of the Good Clinical Practice (GCP) Clinical Center of Xiyuan Hospital who is independent of the study will use SAS 9.2 software to perform a block randomization, generating a sequence of 72 random numbers in 1 : 1 allocation between the two groups. In order to conceal the generation, the outcomes will be conducted by another member of GCP Clinical Center using a central randomization; once a patient meets all the criteria, a random number will then be delivered by telephone to the clinical researchers, unblinding only after data is collected for the first phase of the study (see Section 2.9). The number delivered by telephone will determine whether the subject receives the control or experimental therapy. 

Because the color of the STS solution given to the experimental group is unique and challenging to emulate, blinding will be difficult to achieve at the physician and patient levels. In order to minimize biases as much as possible, all other potential sources of information that may reveal treatment allocation to patients (e.g., contents of case report form, patient's random number) will be judiciously guarded. Additionally, the details of treatment allocation will not be disclosed to any patient until the study has concluded, and all study participants will be discouraged from discussing with one another their involvement in the trial. Finally, the clinical researchers will strictly abide by the study's random design and will interact with the patients in each group with as few differences as possible.

Blinding will be maintained at the level of outcome assessment. The individuals performing laboratory blood analyses, data management, and statistical analyses will be independent of the clinical component of the study and will not be provided with any information that may reveal treatment allocation details. 

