### 2.10. Data Management

The principal investigator of this study will collaborate with the director of the GCP Clinical Center of Xiyuan Hospital to schedule and coordinate this clinical trial. The GCP Clinical Center will be responsible for randomizing subjects into treatment groups, monitoring research progress, managing the data, and performing statistical analyses. All those involved in these aspects of the trial will remain blind to the details of treatment allocation.

All patient data will be recorded by trained clinical researchers using a standardized, preprinted, and paper case report form (CRF). Collection, transportation and preservation of all blood samples will be performed by trained staff using a standardized procedure. The Laboratory of Cardiovascular Diseases at Xiyuan Hospital will analyze all blood samples and report all results to the clinical researchers for documentation. At the conclusion of the study, CRFs will be delivered to the GCP Clinical Center and examined for completeness by an individual unassociated with the data collection process. If complete, the CRF will be closed to further revision in preparation for data entry.

At the GCP Clinical Center, a data manager uninvolved with subsequent statistical analysis for the study will be responsible for overseeing data entry. To ensure the reliability of the recorded data, two individuals under the data manager will each independently input a copy of the CRF data into a special database (EpiData 3.1 software, http://www.epidata.dk/). If any data in the CRF is unclear, the data manager will submit a clarification form to the principal investigator of the study, who will then issue an inquiry for the clinical researchers to resolve as soon as possible. The data manager will confirm the correct data according to the clinical researchers' response.

A third individual under the data manager will proofread the two independently completed database records to ensure that they are identical and accurately represent the data in the CRF. If the database records are not identical, the data in question will be confirmed from the original CRF. Once complete, the database records will be locked to further revision.

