Several limitations affect the strength of our study design. Due to the unavailability of data needed to perform an *a priori* calculation, we determined the sample size for this study by adopting the number used in a comparable trial that we previously completed [14]. As a result, it is possible that our current study design may have insufficient power to reveal statistical significance at the level we desire. In addition, because the color of the STS solution makes double-blinding difficult, our study will be subjected to potential expectation biases from both clinical researchers and study participants. We will attempt to minimize these biases by maintaining blinding at the patient level to the fullest extent possible and by having clinical researchers interact with all subjects as similarly as possible. Full blinding will be maintained at the data analysis level. Finally, our project represents a single-center study and our results may not be wholly generalizable due to a possible selection bias. In the future, multicenter double-blinded, randomized controlled trials are necessary in order to faithfully establish the potential of STS-statin integrative therapy in treating CHD.

Nevertheless, the results of this trial are expected to clarify the potential of an East-West integrative therapy involving STS and simvastatin in reducing atherosclerotic inflammation in CHD patients. Our results will additionally confirm the safety and efficacy of this integrative therapy in treating CHD. Finally, the protocol of our study will also provide a methodological foundation upon which future clinical studies of integrative medicine may develop. 

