## Figures and Tables

**Figure 1 fig1:**
[figure not shown]
Study flowchart.

**Table 1 tab1:** Data Collection Phases and Scheme.

Data collection phase	Phase I: pretreatment 0 day	Phase II: posttreatment 14 days	Phase III: posttreatment 30 days
Inclusion/exclusion criteria	*√*		
Signed informed consent	*√*		
Patient interview			
General health	*√*		
Past medical history	*√*		
Signs and symptoms of present illness	*√*	*√*	*√*
Current medications	*√*	*√*	*√*
Physical exam			
Tongue and pulse examination	*√*	*√*	*√*
Heart rate and blood pressure	*√*	*√*	*√*
Laboratory tests			
Routine blood, urine, and stool (+ occult blood)	*√*	*√*	
Liver and kidney function	*√*	*√*	
Blood lipid and glucose	*√*		
Coagulation	*√*	*√*	
High-sensitivity CRP	*√*	*√*	*√*
Cardiac markers: CK-MB, cTnT, cTnI	*√*		
Electrocardiogram	*√*	*√*	
Inflammatory markers*	*√*	*√*	*√*
Assessment using TCM and Western medicine	*√*	*√*	*√*
Angina and BSS score	*√*	*√*	*√*
Randomization into treatment groups	*√*		
Overall evaluation			
Evaluation of efficacy		*√*	*√*
Evaluation of compliance		*√*	*√*
Evaluation of safety and side effects		*√*	*√*

*NOTE: blood sample will be stored for analysis at the end of the study. Inflammatory markers include interleukin-6 (IL-6), tumor necrosis factor alpha (TNF*α*), vascular cell adhesion molecule (VCAM-1), CD40 antigen and CD40 ligand (sCD40L), monocyte chemotactic protein-1 (MCP-1), and matrix metalloproteinase-9 (MMP-9).

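### Researchers who can know the allocation judge efficacy at Phase II and may hold the patient's Phase II hsCRP result before making the Phase III angina and BSS scores

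*Protocol article*

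**What the plan says.** **The evaluation.** Section 2.9 of the protocol article states for Phase II: "A preliminary, nonstatistical evaluation of treatment safety and efficacy will also be performed by the data collectors". For Phase III it says that "treatment safety and efficacy will again be preliminarily evaluated", without naming the evaluator. Table 1 ticks the row "Evaluation of efficacy" at both visits. Angina and BSS are scored at all three phases.

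**Who collects the data, and what they know.** Section 2.10: "All patient data will be recorded by trained clinical researchers". Section 2.5: once a patient qualifies, "a random number will then be delivered by telephone to the clinical researchers", and that number decides the therapy. The same section concedes that "blinding will be difficult to achieve at the physician and patient levels".

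**Where results go.** Under section 2.10 the laboratory is to analyze the samples and "report all results to the clinical researchers for documentation". The case report forms pass to the GCP Clinical Center only when the study has concluded. They are closed to revision after a completeness check there.

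**What is admitted.** The Discussion, writing about the color of the STS solution, says that "our study will be subjected to potential expectation biases from both clinical researchers and study participants". It does not mention the preliminary efficacy evaluation or the return of laboratory results.

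**The concern.** Angina and BSS scores rest partly on judgement and on what the patient reports. A scorer who knows the arm is already open to expectation bias, and because of the color of the infusion the authors can do little about that among clinical staff.

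The plan then adds two things that the color does not force on it. It asks those staff to form a view of efficacy at the end of treatment, and it sends them the hsCRP result, which is the primary outcome. A researcher who knows that a patient received STS, has seen hsCRP fall and has judged the treatment effective may score that patient's symptoms more favorably 30 days later. What is at stake is the credibility of the Phase III symptom comparison, which is part of the trial's secondary evidence of efficacy.

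**Working it through.** No formula or sample-size figure is involved. The check is whether the sections, read together, leave a route from post-baseline results to the symptom scores.

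1. **Are the data collectors unblinded?** Section 2.10 makes clinical researchers the people who record the data. Section 2.5 gives clinical researchers the allocation. Both use a role name, so the sections show that collectors *can* know the arm. They do not show that every scorer took the telephone call.
2. **Does the blinding statement cover the scorers?** Section 2.5 claims blinded outcome assessment, but the staff it lists are those doing laboratory analysis, data management and statistics. Whoever scores angina and BSS is not on that list.
3. **Which results could be known at the Phase III scoring?**

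| Result | When obtained (2.3, 2.9, Table 1) | Available at Phase III scoring? |
|---|---|---|
| Phase I hsCRP | Before treatment; needed for eligibility | Yes, but carries no information on response |
| Phase II hsCRP | End of the 14-day treatment | Possible: 30 days pass before Phase III |
| Phase II routine tests and ECG | End of treatment | Possible |
| Phase III hsCRP | Same visit as the scores | Possible only if scoring is late or is revised |
| Seven ELISA markers | Stored, assayed at study end | No |

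   The timing of result return is not stated. However, hsCRP between 3 and 15 mg/L is an entry criterion, so at baseline the result must come back before randomization. Only the ELISA samples are described as held for later assay. Nothing delays the Phase II hsCRP report until after Phase III.
4. **Are the scores protected once written?** The article gives no closing step for the forms before they reach the GCP Clinical Center, and no rule that scoring precedes sight of the results.
5. **Which direction can the influence run within a patient?** The Phase II evaluation precedes the Phase III scores, so that path exists. The Phase III evaluation falls at the last scheduled visit, so it has no later score of that patient to affect.
6. **Which outcomes are exposed?** The angina and BSS scores are. The hsCRP measurement is not, because section 2.5 describes the laboratory staff as independent and without allocation information.

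**The case against.** The strongest reply is that the harmful sequence is pieced together and not stated. Section 2.9 does not say that the evaluation uses laboratory results. Section 2.10 gives documentation as the reason for returning them. The scorer is not named, and at Phase I experienced TCM physicians do the tongue and pulse examination that feeds the BSS score. A clinician who knows the arm and scores angina at Phase II has already seen whether the patient improved, so removing a formal efficacy judgement does not remove that knowledge. The added bias may be small beside the basic weakness of unblinded scoring, in a trial that calls itself a pilot.

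Most of this stands, and it limits the claim to what *may* be known. It does not remove the routing: all results go to staff who can know the arm, with open forms and no ordering rule.

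A reader might also infer more than the article supports:

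- **A running unblinded interim look at efficacy.** Ten volunteers between November 2012 and February 2013 is 10/4 = 2.5 to 10/3 ≈ 3.3 a month if that span is taken as three to four months. At that pace, 72 patients take about 72/3.3 ≈ 22 to 72/2.5 ≈ 29 months, so many patients would be scored after others had been evaluated. But the text does not say that evaluations are pooled across patients. The Table 1 row sits beside compliance and safety and reads at least as naturally as a per-patient visit assessment.
- **A pointless task that should be struck out of Table 1.** A condensed article need not state the purpose of the evaluation or any stopping rule. The row may also be where the secondary symptom improvement is recorded.
- **Bias from the other inflammatory markers, or in the hsCRP measurement.** The first are assayed too late to inform any score, and the second is done by staff described as blinded.

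**Conclusion.** The concern holds in a limited form. Sections 2.5, 2.9 and 2.10 together let clinical researchers who can know the allocation judge efficacy at Phase II, and possibly hold the Phase II hsCRP result, before the Phase III angina and BSS scores are made. This is an avoidable addition to the unblinding that the Discussion concedes.

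It rests on two assumptions: that the people who score belong to the clinical researchers named in section 2.10, and that Phase II hsCRP is reported within the 30 days before Phase III. The article supports both without stating either.

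The size of the bias cannot be derived. Its reach is the Phase III symptom scores of every patient who attends that visit, at most 72. Scores at Phase II or III could also be affected by that visit's own results if they are made or revised after those results arrive. The point is worth acting on because the remedy is cheap, not because a large effect has been shown.

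**What to change.** - **Section 2.9, order of work.** Require the angina and BSS scores to be completed and closed on the case report form before any laboratory result from that visit is seen.
- **Section 2.10, routing.** Have the laboratory send Phase II and III hsCRP directly to the GCP Clinical Center. Routine safety results continue to go to the clinical researchers. The ordering rule alone would not keep the Phase II hsCRP from a scorer at Phase III, so both changes are needed. The ELISA results need no new route for this purpose.
- **Section 2.9, preliminary evaluation.** Limit the data collectors' task to safety and compliance, or defer the efficacy judgement until the scores are closed. Keep any Table 1 efficacy entry that records the secondary symptom outcome.

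**Cost.** No extra staff are needed, and no planned measurement is dropped. The clinical researchers would not routinely see the study hsCRP after Phase I. Exclusion criterion (4) in section 2.3, which covers patients whose markers may not reflect atherosclerotic inflammation, would then have to be reviewed from clinical signs and routine tests, or by someone blind to allocation. The protocol should say which. These changes do not make the scorers blind; they only remove the part of the exposure that the infusion's color does not force.

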### 2.10. Data Management

The principal investigator of this study will collaborate with the director of the GCP Clinical Center of Xiyuan Hospital to schedule and coordinate this clinical trial. The GCP Clinical Center will be responsible for randomizing subjects into treatment groups, monitoring research progress, managing the data, and performing statistical analyses. All those involved in these aspects of the trial will remain blind to the details of treatment allocation.

All patient data will be recorded by trained clinical researchers using a standardized, preprinted, and paper case report form (CRF). Collection, transportation and preservation of all blood samples will be performed by trained staff using a standardized procedure. The Laboratory of Cardiovascular Diseases at Xiyuan Hospital will analyze all blood samples and report all results to the clinical researchers for documentation. At the conclusion of the study, CRFs will be delivered to the GCP Clinical Center and examined for completeness by an individual unassociated with the data collection process. If complete, the CRF will be closed to further revision in preparation for data entry.

At the GCP Clinical Center, a data manager uninvolved with subsequent statistical analysis for the study will be responsible for overseeing data entry. To ensure the reliability of the recorded data, two individuals under the data manager will each independently input a copy of the CRF data into a special database (EpiData 3.1 software, http://www.epidata.dk/). If any data in the CRF is unclear, the data manager will submit a clarification form to the principal investigator of the study, who will then issue an inquiry for the clinical researchers to resolve as soon as possible. The data manager will confirm the correct data according to the clinical researchers' response.

A third individual under the data manager will proofread the two independently completed database records to ensure that they are identical and accurately represent the data in the CRF. If the database records are not identical, the data in question will be confirmed from the original CRF. Once complete, the database records will be locked to further revision.

### 2.11. Statistical Analysis

Statistical analyses will be performed using SPSS 15.0 software (SPSS, Inc., Chicago, IL, USA). A Student's *t*-test or Wilcoxon rank-sum test was used, as appropriate, for the analyses of intergroup differences of measurement data; *χ*
^2^ test or Fisher's exact test if necessary was used for comparison of enumeration data. All tests were two tailed and a statistical probability of <0.05 was considered significant. 

## 3. Discussion

Despite recent advances in the treatment and prevention of cardiovascular diseases, CHD remains a significant threat to global health. The use of intensified lipid-lowering therapy involving statins and other Western medications has been proposed in an effort to reduce residual cardiovascular risk [18]. The multinational JUPITER trial, however, clearly demonstrated that patients with healthy LDL-C levels according to standard guidelines may still be at elevated risk due to inflammation associated with atherosclerosis, as measured by hsCRP [19]. Controlling inflammation may therefore be critically important in the treatment of CHD, and to this end, our study will explore the effect of an East-West integrative therapy involving STS and simvastatin on elevated levels of inflammatory markers in CHD patients.

The inflammatory process of atherosclerosis begins when excess LDL particles accumulate in the arterial intima and undergo oxidative modification [20, 21], resulting in recruitment of circulating monocytes via factors including MCP-1 and VCAM-1 [22–24]. In the vascular subendothelium, the monocytes differentiate into macrophages and then become foam cells after endocytosis of the oxidized LDL complexes [25]. Expansion of the inflammatory reaction occurs as these lipid-laden foam cells form the necrotic core of the developing atherosclerotic lesion and release proinflammatory cytokines such as TNF*α* that recruit additional monocytes, dendritic cells, mast cells, and T cells to the area [26]. The extensive crosstalk of cytokines induces vascular smooth muscle cells to produce IL-6, resulting in CRP release by the liver via the acute-phase response [27]. The activated smooth muscle cells also migrate into the arterial intima and lay down fibrous deposits [28], ultimately forming the atherosclerotic plaques that contribute to the development of CHD. As the disease progresses, CD40L-mediated stimulation of MMP-9 expression by vascular smooth muscle cells plays a major role in plaque destabilization [29], altogether increasing the risk of plaque rupture and the onset of complications such as ACS. 

Elevated levels of the inflammatory mediators mentioned above may serve as useful tools for gauging a patient's disease state and cardiovascular risk. CRP is widely regarded as the most useful biomarker for assessing atherosclerotic diseases, not only because of its ease and reliability of measurement, its wide and dynamic range of concentrations, and its remarkable stability but also because its degree of elevation in the blood correlates significantly with the level of risk for future adverse cardiovascular events associated with advanced atherosclerosis, such as myocardial infarction and ischemic stroke [27, 30]. Notably, CRP level is not related to the risk of developing venous thrombosis, a vascular condition typically independent of atherosclerosis [30]. Moreover, Liuzzo et al. found that although CRP levels are significantly increased in patients with unstable angina, which is usually caused by CHD due to atherosclerosis, the biomarker's concentration is not elevated in patients with variant angina, which is caused not by atherosclerosis but by vasospasms of the coronary arteries [31]. These observations altogether suggest that, in the context of cardiovascular disease, the extent of CRP elevation predicts the extent of atherosclerotic inflammation, thereby making CRP level a suitable primary outcome parameter for our study.

The levels of IL-6, TNF*α*, VCAM-1, CD40, sCD40L, MCP-1, and MMP-9 were selected as secondary outcome parameters in this trial, as these inflammatory markers are less effective indicators of atherosclerotic disease status compared to CRP. Tayebjee et al. found that levels of sCD40L and MMP-9 are significantly higher in stable CHD patients than in healthy controls but also that these markers may not strongly predict the severity of CHD [32]. In addition, although Biasucci et al. found that elevated IL-6 levels predict worse prognosis in patients with unstable angina, the authors were able to detect IL-6 in only 61% of their unstable angina group [33]. Nevertheless, the analysis of these inflammatory markers in addition to CRP provides a broader perspective of the inflammatory state of each patient, allowing us to examine and interpret the effect of STS-simvastatin integrative therapy on inflammation reduction with greater depth. 

It is possible that the biomarker concentrations measured in our study may reflect systemic inflammation due to a cause other than atherosclerosis. Indeed, CRP is an acute phase protein released by the liver as part of the body's immune response to nonspecific disturbances, including infection, autoimmune disorders, trauma or surgery, and cancer [34]. To diminish the effect of this possibility, we will carefully consider the past and present medical histories of all eligible patients before enrollment and exclude any patients in whom inflammatory markers may not accurately reflect the state of CHD. Additionally, we will also monitor all study participants during the course of the trial for changes that may confound interpretation of biomarker data, such as acquisition of a nosocomial infection. 

The mechanisms by which tanshinone IIA and statins inhibit the inflammatory process of atherosclerosis are diverse, numerous, and in many cases shared (reviewed in [8, 35]). Using STS and simvastatin in combination may yield an additive, supplementary effect not only in the reduction of internal inflammation but also in the improvement of external symptoms associated with CHD. In this trial, we will examine the therapeutic efficacy of a STS-simvastatin integrative therapy in CHD patients by quantitatively scoring each study participant's angina and BSS symptoms and examining for any changes over the course of the trial. 

There is a risk for negative interactions in any combination drug therapy, but integrative treatments involving STS appear to be relatively safe. In a systematic review of 25 randomized controlled trials, Qiu et al. found that integrative therapies involving STS for unstable angina may produce fewer side effects than the component Western therapies alone [36]. Side effects that were associated with the integrative therapies included flushing, dizziness, bruising, gum bleeding, blood in the sputum, and swelling at the STS injection site, but none were considered severe and none resulted in discontinuation of treatment. Another clinical study, which used STS and simvastatin in combination to treat peripheral vascular disease also found the integrative treatment to be safer than the statin therapy alone [10]. Our study will continue to monitor the short- and long-term side effects of STS-simvastatin integrative therapy and verify the safety observations reported by previous trials.

Several limitations affect the strength of our study design. Due to the unavailability of data needed to perform an *a priori* calculation, we determined the sample size for this study by adopting the number used in a comparable trial that we previously completed [14]. As a result, it is possible that our current study design may have insufficient power to reveal statistical significance at the level we desire. In addition, because the color of the STS solution makes double-blinding difficult, our study will be subjected to potential expectation biases from both clinical researchers and study participants. We will attempt to minimize these biases by maintaining blinding at the patient level to the fullest extent possible and by having clinical researchers interact with all subjects as similarly as possible. Full blinding will be maintained at the data analysis level. Finally, our project represents a single-center study and our results may not be wholly generalizable due to a possible selection bias. In the future, multicenter double-blinded, randomized controlled trials are necessary in order to faithfully establish the potential of STS-statin integrative therapy in treating CHD.

Nevertheless, the results of this trial are expected to clarify the potential of an East-West integrative therapy involving STS and simvastatin in reducing atherosclerotic inflammation in CHD patients. Our results will additionally confirm the safety and efficacy of this integrative therapy in treating CHD. Finally, the protocol of our study will also provide a methodological foundation upon which future clinical studies of integrative medicine may develop. 

